**Table 11.3.2.7. SAE contact**

| Unit | Contact | Telephone/Fax |
| --- | --- | --- |
| Sun Yat-sen University Cancer Center | Ethics Committee | [name] |
| Chia Tai Tianqing Pharmaceutical Group Co., Ltd. | Medical Affairs | [name] |
| State Food and Drug Administration Drug  Registration Division | | [name]/[name] |
| Division of Medical Care, Department of  Medical Administration, Ministry of Health | | [name] |

- - 1. **Process for unblinding**

Investigators are not permitted to unblind if there is a necessary medical reason arises. Unblinding will only be granted by the study center director and principal investigator in case of an emergency such as SAE. The investigator should inform the CRA, the medical director of the sponsor, and the ethics committee to log into the BioKnow-RTS system if blindness is broken. The date, subjects, reason, and process for unblinding must be recorded in the EDC and simultaneously reported to the SAE.

- 1. **Drug resistance mechanisms**

This study will perform a multigene test (10 mL of peripheral blood each time before treatment, at the first efficacy evaluation, and at the time of tumor progression) on the peripheral blood of patients by QiYuan 329 gene panel (OrigiMed, Shanghai, China) for monitoring the resistance mechanism of targeted therapy

1. Ethical Considerations and Informed Consent
   1. **Ethical considerations**

The protocol is approved by the ethical committee of Sun Yat-sen University Cancer Center. The sponsor and the investigator should provide documents such as Application Form for Ethical Review, List of Clinical Trial Study Team Members, Certificate of Analysis, Sample of Informed Consent, Phase I Clinical Trial Protocol, CRF, and Investigator's Brochure. This trial will be conducted in accordance with the ethical principle of the Declaration of Helsinki (version 1996), GCP issued by CFDA, and related regulations. The investigator will not begin any study subject activities until approval from the Clinical Research Ethics Committee of the Clinical Trial Team leader. Any modifications of the protocol during the clinical study should be declared and filed to the ethics committee.

- 1. **Informed consent**

Subjects must provide informed consent to participate in this trial before receiving treatment in this trial to guarantee their legal rights. It is the responsibility of the investigator to provide an adequate explanation in understandable language of the aims, importance, anticipated benefits, potential hazards, and consequences of the study. If the subjects and their legally acceptable representative (LAR) are unable to read/write, then an impartial witness should be present during the entire informed consent process and must append his/her signatures to the consent form on that day. Informed consent documents must be marked version and date or modification date.

1. Sponsor/Investigator Responsibilities

To ensure the quality processes, the sponsor and investigator should strict adherence to GCP.

- 1. **Sponsor**

(1) Clinical research associates (CRA) will provide the investigator with the investigator’s brochure or drug instructions and explain the protocol and eCRF completion to the investigator before clinical initiation. The clinical supervisor is responsible for clinical monitoring and regular visits, with the following visit frequencies: At least one visit per cycle for the first 4 cycles; At least one visit every 2 cycles after 5 cycles.

(2) CRA should ensure that they can keep in touch with the investigator at any time by telephone, fax, and mail.

- 1. **Investigator**

(1) Investigator must responsible for obtaining an informed consent form signed by each subject or their representative.

(2) Investigators must seriously follow the requirements to fill out eCRF.

(3) Investigator must actively cooperate with CRA for regular visits.

(4) Investigator must ensure the completeness of laboratory records, clinical records, and original medical records.

1. Data Management
   1. **Data collection**

In this protocol, the eCRF is used for clinical research data capture, and study staff member whose training in this function are authorized to log in to the electronic data capture (EDC) system. The PI or designated clinical research coordinator (CRC) should enter the data into the EDC system in accordance with the follow-up requirement and eCRF completion guide logical verification procedure implemented in the system typically runs data check to assure the completeness and logicality of the study-related records in EDC system and notice the eCRF entry error (if any), and PI or the CRC can make appropriate corrections and explanation. The PI will get CD-ROM or certified copy containing the patient data after the database is locked for record-keeping.

The investigator is ultimately responsible for data collection and report of all clinical and laboratory data recorded in the eCRF and other data collection forms (original records), to assure the attributable, legible, contemporaneous, original, accurate, enduring, complete, and consistent.

The eCRF is required to be signed by the investigator or the investigator’s designated representative and data recorded in eCRF needs to be verified to ensure credibility. Any change or correction to an eCRF and source documents should be dated, signed, and explained (if necessary), and should not obscure the original entry.

As a rule, the original record is the diagram of the hospital or doctor, and data collected by eCRF should be consistent with them. In some instances, however, the capture of study data as the original record can also be performed by eCRF and should be archived by the research institution for accurate documentation.

- 1. **Statistical analysis**
     1. **Analysis datasets**

1. Full analysis set (FAS)

FAS included all randomly allocated patients who were treated with at least one dose of the study drug and received at least one post-treatment efficacy assessment, according to the intention to treat (ITT) principle. No imputation of missing data.

1. Per-protocol set (PPS)

PPS will be defined as all subjects who met the trial protocol, did not take prohibited drugs, with favorable compliance, and completed CRF. No imputation of missing data. Efficacy analysis was conducted based on PPS populations.

1. Safety analysis set (SS)

The SS population will serve as the population for the safety analysis. All randomized subjects have received at least one dose of the research drug and have a post-administration safety record.

- - 1. **Statistical analysis plans**

All statistical analysis will be performed using the SAS statistical package (≥9.3 version) with a two-sided test. P ≤0.05 is considered significant, with 95% confidence intervals (CI).

1. Baseline

Quantitative data including age, height, weight, and so on are described as mean ± standard deviation (SD), median, maximum, and minimum values, and qualitative data such as gender and ECOG score are reported by number and frequency.

1. Efficacy assessment

The primary endpoint of this trial, PFS, will be estimated using the Kaplan-Meier method with a 95% CI and presented with the Kaplan-Meier curve. The comparison of PFS between intervention arms will be performed using a stratified log-rank test. The HR and the corresponding 95% CI will also be provided based on a Cox proportional hazard model, using such as age, ECOG PS, and EGFR mutations (exon 19 deletions or an exon 21 mutation) as stratification factors.

The secondary endpoint such as OS, TTPD, and DoR will be analyzed in the same method as the primary endpoint. The cochran-mantel-haenszel (CMH) method or Chi-square test will be used to compare ORR and DCR between the groups, and Fisher's exact test method will be used to calculate ORR, DCR, and 95% CI. The Student t-test or Wilcoxon rank sum test will be used to compare the QoL between the groups.

1. Safety analysis

Safety analysis will be mainly descriptively summarized and the mean or incidence of pre- and post-administration examination tests (if necessary). Vital signs, physical examination, and laboratory tests will be demonstrated mainly through the changes from baseline in clinical and the incidence of abnormalities. All AEs will be coded using the Medical Dictionary for Regulatory Affairs (MedDRA) for safety analysis. Summary and compare the incidence of all AEs, treatment-emergent adverse events (TEAEs) with grade 3 or more, serious TEAEs, and so on between two intervention arms will be tabulated according to MedDRA PT and primary system organ class (SOC), as well as CTCAE grading.

- 1. **Interim analysis**

The interim analysis will be conducted by IDMC and will conduct 1-2 analyses. The IDMC will analyze the safety and efficacy data (PFS) and advises on the study conducted by the results of interim analyses. The IDMC, consisting of 3-4 independent oncologists and one independent statistician, is independent of the sponsors and investigators.

- 1. **Data storage**

All documents must be archived by the investigator. According to the requirements of GCP, data will be stored under lock and key for 5 years.

- 1. **Publication policy**

All data will be published only with the consent of the PI.

References

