**Figure 3. Effect of food on the pharmacokinetics in healthy subjects**

**Table 6. Effect of food on the pharmacokinetic parameters in healthy subjects**

| **Pharmacokinetic parameters** | **High-fat diet group** | **Fasting group** |
| --- | --- | --- |
| C_max_ (ng·mL^-1^) | 3.35 ± 1.35 | 3.90 ± 1.60 |
| T_max_ (h) | 10.5 ± 6.7 | 9.3 ± 5.1 |
| AUC_last_/AUC_0-t_ (ng·h·mL^-1^) | 308 ± 120 | 377 ± 134 |
| AUC_inf_/AUC_0-∞_ (ng·h·mL^-1^) | 392 ± 145 | 486 ± 158 |
| MRT_last_/MRT_0-t_ (h) | 83.7 ± 6.8 | 86.0 ± 6.5 |
| MRT_inf_/MRT_0-∞_ (h) | 153.2 ± 43.7 | 161.7 ± 41.3 |
| t_1/2_ (h) | 107.2 ± 27.4 | 113.2 ± 30.3 |

- 1. **Clinical study**

As of April 2018, phase II and III clinical studies of anlotinib have been conducted in multiple indications, including medullary thyroid cancer, differentiated thyroid cancer, soft tissue sarcoma, NSCLC, small cell lung cancer, renal cancer, neuroendocrine tumor, colorectal cancer, liver cancer, gastric cancer, and phase I indication exploration. For detailed information on relevant clinical studies, please refer to the Investigator's Manual.

1. Study Objective

To observe and evaluate the efficacy and safety of anlotinib combined with gefitinib in patients with stage IIIB-IV EGFR-mutated NSCLC.

1. Study Design
   1. **Study design**

This study is a multicenter, randomized, double-blind, placebo-controlled, parallel clinical trial to evaluate the efficacy and safety of gefitinib combined with anlotinib as first-line treatment in patients with stage IIIB-IV EGFR-mutated NSCLC.

In the absence of withdrawal of consent, intolerable side effects, or a decision by the investigator to be inappropriate for further trial, treatment is continued for each subject until radiographically confirmed disease progression. The efficacy and safety indices are observed during the study.

- 1. **Type of comparison**

This study is a parallel, placebo-controlled study, and its type of comparison is a superiority trial.

PFS is used as a primary endpoint in this study. If the HR of the PFS comparison between the two groups is statistically significant and clinically significant, the study drug is considered superior to the placebo.

- 1. **Estimating sample size**

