7. Pregnant or lactating women; A fertile patient who is unwilling or unable to use effective contraception;
8. The investigator identifies other conditions that may affect the proceeding of the clinical study and its outcomes.
   1. **Dropout/removal criteria**
9. Patients who failed to meet the inclusion criteria;
10. Safety evaluation could not be performed without one dose of the drug;
11. Both modern Chinese medicine and immunomodulators approved by SFDA are simultaneously used for the treatment of lung cancer;
12. The dose, method, and course of treatment are not specified according to the study protocol.
    1. **Termination criterion**
13. Withdrawl of informed consent and request to withdraw from the study;
14. Radiographic evidence of disease progression;
15. Pregnancy events occurred during the study;
16. Subjects who were still unable to tolerate toxicity after dose adjustment;
17. Decisions to withdraw from study by the sponsor.
18. Study Drugs
    1. **Overview of drugs**
       1. **Drug information**

Study Drugs are produced by Chia Tai Tianqing Pharmaceutical Group Co., Ltd., and the detailed information is shown in Table 6.1.1.

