**PFS**

PFS is defined as the time from randomization to the first time of disease progression or death from any cause, whichever occurs first. If the subject did not experience disease progression or death, then PFS was defined as the date of the last confirmed progression-free. Patients who discontinued for reasons other than disease progression (no subsequent tumor image) and starting the therapy after the trial were censored at the time of discontinuation or initiation of treatment. In cases other than those described above, pre-planned sensitivity analyses will undertake to define PFS based only on the date of confirming tumor progression events. New onset other tumor is not considered indicative of PD and is not censored as data.

If the image examination and evaluation show progression, the data of disease progression is not the time showing signs of disease progression, but the time of the development of radiologically noticeable PD.

- - 1. **The secondary endpoints**

**OS**

OS is defined as the time from the randomization data to the date of death due to any cause. OS is censored at the date of the last visit for those still alive at the time of the last visit. Patients lost to follow-up were censored at the time of the last contact. Censored OS is defined as the time from randomization to censor.

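### Efficacy in a superiority trial is assigned to the per-protocol set, and the full analysis set labelled as intention-to-treat omits undosed and unassessed patients, so neither set compares the groups as randomised

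*Protocol*

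**What the plan says.** Section 3.2 fixes the purpose: "This study is a parallel, placebo-controlled study, and its type of comparison is a superiority trial". Section 10.1 fixes the endpoint: "PFS is defined as the time from randomization to the first time of disease progression or death from any cause".

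Section 13.2 defines three sets.

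- **The PPS (per-protocol)** is described in these terms: "PPS will be defined as all subjects who met the trial protocol, did not take prohibited drugs, with favorable compliance, and completed CRF". The definition closes with "Efficacy analysis was conducted based on PPS populations".
- **The FAS (full analysis)** has a dosing condition: "FAS included all randomly allocated patients who were treated with at least one dose of the study drug". Its second condition is that these patients also "received at least one post-treatment efficacy assessment, according to the intention to treat (ITT) principle".
- **Safety set:** used for safety only.

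The FAS and PPS entries both add "No imputation of missing data". The sentence on the PPS is the only one in the protocol that ties efficacy to a set. The statistical part of the synopsis, section 3.2, section 10.1 and the analysis-method text in 13.2 name no set for PFS or OS, and the FAS is given no analysis.

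Section 5.4 lists, among its dropout and removal criteria, "The dose, method, and course of treatment are not specified according to the study protocol".

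**The concern.** In a superiority trial the protection against bias comes from comparing everyone who was randomised, in the arm to which they were allocated. Compliance, use of prohibited drugs and completion of the CRF arise after randomisation, and an added active drug can influence them. A comparison restricted on them can mix the drug's effect with selection.

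The FAS does not repair this. Under section 10.1, death from any cause counts from randomisation. A patient who dies before any efficacy assessment has the primary event but is not in the FAS. A patient who is never dosed is also left out. The endpoint definition and the set definition therefore contradict each other, and the intention-to-treat label hides it. For ORR and DCR, leaving out patients without an assessment shrinks the denominator.

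At stake is whether the phase III PFS claim rests on the randomised comparison. The question cannot be left to an SAP, because the protocol itself states the rule.

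**Working it through.** **1. The plan's own figures reproduce.** Inputs from section 3.3: median PFS 15 and 10 months, two-sided alpha 0.05, power 0.80, 1:1 allocation, 18 months' accrual plus 18 months' follow-up, 20% dropout.

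- HR under exponential PFS = 10/15 = 0.667.
- Schoenfeld events = 4 × (1.96 + 0.84)² / (ln 0.667)² ≈ 191; the plan states 192.
- Power at 192 events = Φ(√192/2 × 0.4055 − 1.96) = Φ(0.849) = 0.802.
- Event probabilities with uniform accrual are 0.704 and 0.836. With 124 per arm this gives 87.4 + 103.7 ≈ 191 events (stated 88 + 104 = 192).
- 248 / 0.80 = 310.

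The sample size is not in dispute.

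**2. Follow a randomised patient through the definitions.**

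- Dies before the first assessment: PFS event (10.1), not in the FAS (13.2).
- Never dosed: PFS clock running from randomisation (10.1), not in the FAS.
- Assessed, but poorly compliant or with an incomplete CRF: in the FAS, not in the PPS, and so outside the set named for efficacy.

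**3. How large could the FAS effect be?** The protocol gives no exclusion rates, so these are assumptions. Simulation with 155 per arm, 18 + 18 months and medians 15 and 10 months, adding a share of failures before week 6 and fitting a Cox model with and without them:

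| Early failures, experimental / control | HR, all randomised | HR, early failures excluded |
|---|---|---|
| 3% / 1% | 0.69 | 0.67 |
| 5% / 2% | 0.70 | 0.67 |
| 5% / 5% | 0.68 | 0.66 |

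The shift comes mainly from imbalance between the arms.

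**4. The same check with no true effect.** True HR 1, 155 per arm, 4,000 runs. Under a 10-month median, 1 − exp(−ln 2 × 1.38/10) = 9.1% of patients fail within 42 days.

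- Excluding half of these failures in both arms: HR 1.00, one-sided error 0.026 (nominal 0.025).
- Excluding half of them in the experimental arm only: HR 0.95, one-sided error 0.061.

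One-armed exclusion is a deliberate extreme, shown only to mark the range.

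**5. The PPS.** Its exclusions cannot be quantified from the protocol. No figure is offered.

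**6. After the fix.** 192 events still give 80.2% power. They require 192/310 = 61.9% of all randomised patients to have an event, against 192/248 = 77.4% in the plan's calculation. If nobody were lost, 155 × (0.704 + 0.836) ≈ 239 events would be expected by month 36.

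**The case against.** The sentence on the PPS says neither that it is the only set nor that it is the primary one, so a supportive FAS analysis is not ruled out. That is true, but none is assigned, and the FAS has its own gap. Several stronger readings are tempting and do not hold.

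- *Patients who stop for toxicity before week 6 leave the analysis.* Mostly not. Section 9.3 asks for imaging at the end of treatment or withdrawal if none was done within 4 weeks, then continued tumour evaluation for patients without imaging progression. Section 6.2 allows gefitinib to continue after anlotinib stops. Section 9.2 also lists imaging in cycle 1, so week 6 is not consistently the first scan. The FAS mainly loses undosed patients and those who die or are lost with no assessment.
- *Up to 20% (62 of 310) could be dropped from the PPS.* The 20% in section 3.3 is a dropout allowance for sample size. It is neither a PPS exclusion rate nor a bound on one.
- *The bias favours the experimental arm.* It may. Under the plan's own medians, failures within 42 days are commoner in the control arm: 9.1%, against 1 − exp(−ln 2 × 1.38/15) = 6.2%. Equal exclusion leaves the null HR at about 1.00.
- *The gain in significant results can be read off the simulation.* It follows all 310 patients to month 36, whereas the synopsis sets the final analysis at about 192 events. At 192 events, HRs of 0.705 and 0.735 (the latter from an assumed 8% / 2%) give Schoenfeld power of about 68% and 57%, so month-36 significance rates do not describe the planned analysis.
- *Section 5.4 removes patients from the efficacy analysis.* It does not say so. Its effect on the analysis sets is only unclear.
- *The trial is no longer randomised.* Allocation remains random. What is lost is the comparison of the groups as allocated.

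**Conclusion.** The point stands as a fault in what the protocol states. The only set tied to efficacy is selected on post-randomisation behaviour, and the set described as intention-to-treat leaves out some randomised patients, including some with a primary-endpoint event. Neither compares the groups as randomised.

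Bias is possible if exclusions differ between arms; the protocol gives no rates from which to settle its size or direction. At an assumed 5% versus 2% of early failures, the HR moves from about 0.70 to 0.67; at equal rates the change is small. These figures concern the FAS only and rest on exponential PFS and the assumed rates. Because the primary claim depends on the analysis set and the correction is mostly wording, it should be made before the efficacy analysis.

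**What to change.** - **Section 13.2:** make all randomised patients, analysed as allocated, the primary set for PFS and OS and the denominator for ORR and DCR, with non-evaluable patients counted as non-responders. Replace the sentence that bases efficacy on the PPS so that the PPS is a sensitivity analysis. Either redefine the FAS as all randomised patients or drop the intention-to-treat label from its present definition.
- **Section 10.1:** state that a death before the first scan is an event on the date of death. Settle the censoring of living patients without a post-baseline scan. The present text censors those who discontinue without later imaging at discontinuation or at the start of new treatment; if censoring at randomisation is preferred, that text must be amended.
- **Section 5.4:** state that its criteria do not remove patients from the primary analysis.
- **Section 9.5:** survival follow-up now starts after the 30-day visit that follows drug discontinuation, so specify it for patients who were never dosed.

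The cost is wording in these sections, some added follow-up for never-dosed patients, and a possibly less favourable estimate. The event target of 192 and the power of about 80% do not change.
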